## Abstract

**Background:**

Breaking bad news (BBN; e.g., delivering a cancer diagnosis) is perceived as one of the most demanding communication tasks in the medical field and associated with high levels of stress. Physicians’ increased stress in BBN encounters can negatively impact their communication performance, and in the long term, patient-related health outcomes. Although a growing body of literature acknowledges the stressful nature of BBN, little has been done to address this issue. Therefore, there is a need for appropriate tools to help physicians cope with their stress response, so that they can perform BBN at their best. In the present study, we implement the biopsychosocial model of challenge and threat as theoretical framework. According to this model, the balance between perceived situational demands and perceived coping resources determines whether a stressful performance situation, such as BBN, is experienced as challenge (resources > demands) or threat (resources < demands). Using two interventions, we aim to support medical students in shifting towards challenge-oriented stress responses and improved communication performance: (1) stress arousal reappraisal (SAR), which guides individuals to reinterpret their stress arousal as an adaptive and beneficial response for task performance; (2) worked examples (WE), which demonstrate how to BBN in a step-by-step manner, offering structure and promoting skill acquisition.

**Methods:**

In a randomized controlled trial with a 2 (SAR vs. control) x 2 (WE vs. control) between-subjects design, we will determine the effects of both interventions on stress response and BBN skills performance in *N* = 200 third-year medical students during a simulated BBN encounter. To identify students’ stress responses, we will assess their perceived coping resources and task demands, record their cardiovascular activity, and measure salivary parameters before, during, and after BBN encounters. Three trained raters will independently score students’ BBN skills performances.

**Discussion:**

Findings will provide unique insights into the psychophysiology of medical students who are tasked with BBN. Parameters can be understood more comprehensively from the challenge and threat perspective and linked to performance outcomes. If proven effective, the evaluated interventions could be incorporated into the curriculum of medical students and facilitate BBN skills acquisition.

**Trial registration:**

ClinicalTrials.gov (NCT05037318), September 8, 2021.

**Supplementary Information:**

The online version contains supplementary material available at 10.1186/s40359-023-01167-6.

## Background

### Breaking Bad News – an important and stressful communication task

Breaking bad news (BBN) in the medical field refers to the delivery of a serious diagnosis (e.g., cancer diagnosis, stillbirth) from a physician to a patient which is associated with sudden lifechanging consequences for the patient [1, 2]. Not every diagnosis is of the same severity, and how bad news is received by the patient depends on many individual characteristics (e.g., expectations, personality traits, social support) [3]. Therefore, patients’ emotional reactions to bad news can differ greatly—from perplexity, silence, and disbelief to intense displays of anger or sadness—and are thus very difficult for the physician to predict [1, 4]. Even physicians who are frequently confronted with BBN regard it as highly demanding and stressful, and most often feel overwhelmed, uncomfortable, or insufficiently prepared [5–9]. Increased psychophysiological stress levels are observed in physicians during BBN encounters [6, 8]. Importantly, these increased stress levels can already be seen in medical students learning how to BBN in role-play scenarios with simulated patients (SPs) [10, 11]. Increased stress, in return, can impair educational and clinical skills performances (e.g., communication performance) of medical students in particular [12]. When being confronted with a BBN task, stressed physicians might give false hope or even avoid disclosing the bad news [3, 13]. However, it is of utter importance that bad news is delivered appropriately—with empathy while not trivializing unpleasant facts [1]. It has been shown that the way bad news is communicated can affect patient-related outcomes in the long term (e.g., treatment adherence [14–16], recovery [17–19], psychological wellbeing [18, 20]). While a growing body of literature acknowledges the highly stressful nature of BBN and investigates best-practice in BBN (see [8] for a review), further exploration of medical students’ stress responses is needed and tools to help them manage their stress in this context have been widely neglected. Although time-intensive stress management programs have helped students cope with their stress in medical training [21], integrating such programs into the already overloaded curriculum of medical students is problematic. Moreover, such extensive stress interventions can lack acceptance due to the fact that the state of ‘being stressed’ is increasingly seen as normal among medical students and that suffering from it may be viewed as a form of weakness [22]. Hence, there is a need for low-threshold approaches that allow students both to identify stress and to deal with it appropriately without being stigmatized [23].

In the current study, we aim to make a significant contribution to the advancement of research by adopting the biopsychosocial model (BPSM) of challenge and threat as organizing framework to investigate the effects of stress arousal reappraisal and worked example-based BBN learning on the psychophysiological responses and communication skills performance of medical students tasked with BBN to SPs. We first introduce the BPSM of challenge and threat, then the stress arousal reappraisal intervention, and finally, the worked example-based BBN learning.

### The biopsychosocial model of challenge and threat

To understand medical students’ stress responses more holistically, we adopt the BPSM of challenge and threat as theoretical framework [24, 25]. The model builds on the premise that psychological stress states are embodied in measurable activity patterns of the cardiovascular system [26, 27]. The model is further specified to motivated performance situations, which require active (cognitive or behavioral) responses to achieve personally relevant outcomes (e.g., academic examinations, job interviews, public speaking) [24, 28, 29]. The active response and self-relevance lead to task engagement (indexed by an increased heart rate and a reduced pre-ejection period), which is a precondition for, and common across, the challenge-threat continuum [30]. Given task engagement, on the one hand, challenge emerges when individuals perceive their own resources (e.g., knowledge, abilities, familiarity) as higher than the situational demands (e.g., danger, effort, uncertainty). On the other hand, threat occurs when situational demands exceed perceived resources. The evaluation of resources and demands is an automatic and dynamic process (i.e., the evaluation can shift as the situation unfolds) [24, 25, 31, 32]. The resources-demands differential (i.e., perceived coping resources minus perceived task demands) is represented on a bipolar continuum, with challenge and threat as anchors, rather than distinct states. Therefore, relative differences in demands and resources can be interpreted as greater or lesser challenge and threat [33]. A more positive score reflects the task being evaluated as more of a challenge and less of a threat.

An important aspect of the BPSM of challenge and threat is that distinctive cardiovascular patterns manifest in challenge and threat states. Challenge states are accompanied by a lower total peripheral resistance (TPR; an index of net constriction vs. dilation in the vascular system) and increased cardiac output (CO; liters of blood pumped per minute) compared to threat states. In other words, not only does the heart pump more blood but the veins and arteries also expand to improve blood flow, resulting in a more efficient cardiovascular activity. This adaptation does not occur in threat states, meaning that the faster and stronger heart contractions during stress in fact increase TPR while not necessarily affecting CO [30, 34]. Together, the sum of CO and reverse scored TPR define the cardiovascular challenge-threat index. A higher cardiovascular challenge-threat index (higher CO, lower TPR) indicates a more adaptive challenge-oriented stress response. An advantage of the cardiovascular indices of challenge and threat is that they do not depend on an individual’s willingness or ability to accurately report on their appraisals [35, 36].

Recently, there has been increasing interest in understanding how other important physiological systems may vary along the challenge-threat continuum [28, 37]. It has been theorized that both challenge and threat states activate the sympathetic-adrenal-medullary (SAM) axis, whereas the hypothalamic-pituitary-adrenal (HPA) axis might be more responsive to threat states, in anticipation of failure and damage [30, 38–40].

Activation of the SAM axis increases the synthesis and release of catecholamines from the adrenal medulla—particularly epinephrine and norepinephrine—which in return trigger a multitude of cardiovascular adaptations. The main functions are to increase heart rate, reduce pre-ejection period, and constrict veins (to facilitate the return of oxygen-poor blood to the heart) [29]. Epinephrine further mediates adrenergic vasodilation (widening of blood vessels by relaxation of smooth muscles) [41]. These cardiovascular adaptations match the cardiovascular challenge pattern, which is suggested to be governed by the SAM activity. However, a downside of epinephrine and norepinephrine as indices of SAM activity is that they can only be measured reliably by blood taking. In this context, salivary alpha-amylase (sAA)—an enzyme secreted from the acinar cells of the salivary glands—has gained importance as a non-invasive marker for the activity of the locus coeruleus-norepinephrine system and peripheral SAM axis activity [42–46]. Previous research suggests that sAA may well indicate challenge and threat, whereby increased levels of sAA manifest in challenge states, although the authors acknowledge that this has yet to be confirmed by further research [47, 48]. The SAM axis is a fast-acting system and cardiovascular adaptations to stressors occur almost immediately.

In contrast, the main product of the HPA axis is the catabolic hormone cortisol, released from the adrenal cortex. It is theorized that cortisol dampens epinephrine-induced vasodilation, thereby increasing blood pressure when both axes are activated simultaneously [24, 39, 40]. In line with this, individuals in a cardiovascular threat state exhibited higher cortisol reactivity compared to individuals in a cardiovascular challenge state [49]. Activation of the HPA axis during acute stress also triggers the release of the anabolic hormone dehydroepiandrosterone (DHEA), which may play a protective factor during stress reaction and contribute to more favorable behavioral and emotional responses [50–56]. Elevated levels of DHEA compared to cortisol are further associated with resilience and thriving in stressful situations [57–59]. Therefore, the anabolic balance (i.e., the ratio of DHEA to cortisol) between the two hormones is of special interest, as they regulate each other and together could provide a sensitive indicator of challenge and threat [60]. While the HPA axis also responds instantly, observable adaptations and cortisol release take more time to manifest and to return to homeostasis.

To summarize, according to the BPSM of challenge and threat, an initial evaluation of personal resources and situational demands orchestrates downstream stress responses in the context of motivated performance situations (see Table 1). Crucially, previous research suggests that the resources-demands differential is amenable to interventions (e.g., [47, 61–63]) and, as shown in a recent meta-analysis [64], more adaptive challenge states are intertwined with increased task performance. In the present project, we propose stress arousal reappraisal and worked example-based learning interventions, that could be used to achieve more adaptive stress responses and communication performances in the BBN context.

**Table 1 Tab1:** Psychophysiological adaptations depending on challenge and threat

Students in challenge state		Students in threat state
	**Psychological adaptations**	
Perceived coping resources higher than perceived task demands	Resources-demands differential	Perceived coping resources lower than perceived task demands
	**Neuroendocrine adaptations**	
Higher	Anabolic balance (DHEA/Cortisol)	Lower
Higher	sAA	Lower
	**Cardiovascular adaptations**	
Lower	TPR	Higher
Higher	CO	Lower
Better BBN communication	**Performance**	Worse BBN communication

*Note.* DHEA = dehydroepiandrosterone; sAA = salivary alpha-amylase; TPR = total peripheral resistance; CO = cardiac output

### Stress arousal reappraisal

Stress arousal reappraisal (SAR) makes use of the lay belief that stress is inherently negative. Experienced arousal (e.g., increased heart rate) during stressful situations (e.g., when giving a speech) is commonly perceived as debilitative and harmful towards task performance [39]. Consequently, a typical coping approach is to downregulate or eliminate stress arousal altogether [65]. Contrary to this misconception, SAR promotes the often-overlooked positive and adaptive aspects of stress responses and emphasizes an individuals’ agency in the emergence of said response. That is, the way people perceive stress (positive or negative) is in fact decisive to their stress responses [66]. Towards this end, SAR interventions instruct individuals to reinterpret stress arousal as a functional response, which is indeed beneficial for task performance. For instance, an increased heart rate prepares an individual for a demanding situation, by providing additional oxygen to the body and brain. The idea is that the act of defining stress arousal itself as a coping resource will cause a shift in the BPSM framework from threat towards challenge state, and ultimately promote more adaptive stress responses. It is noteworthy that task engagement is essential for reappraisal to thrive; if there is no sympathetic arousal to begin with, then there is nothing to reappraise [67]. In line with the suggested theory, previous research has demonstrated that SAR interventions lead to more efficient psychophysiological stress responses and improved task performance (e.g., [47, 48, 65, 68–71]).

### Worked examples

BBN is a particularly delicate and challenging situation, and therefore devoted training is of utmost importance for physicians to optimize their BBN-performance [72, 73]. The question of how to best teach communication skills remains a core issue for medical schools worldwide [74–76]. We postulate that worked examples (WE) are a suitable approach to teach established BBN communication protocols (e.g., SPIKES, [1]). A worked example usually implies an initial problem (in our case how to BBN to a patient) and provides a step-by-step demonstration of its successful solution (in our case showing a physician BBN by following six steps of SPIKES). WEs are most useful for novice learners with restricted prior knowledge [77]. By breaking down an ill-defined task into individual steps, the complexity of the task, and at the same time, the cognitive load of the learner can be reduced. This allows for an easier acquisition of schemas in long-term memory, which can then be utilized to approach similar problems (e.g., communication of various diagnoses) [78]. Schemas can be retrieved as a single unit from memory despite cognitive constraints that might also occur during BBN [79]. While WE interventions have proven to be effective in well-defined domains such as mathematics and physics [80, 81], more recently, similar effects were demonstrated in ill-defined domains such as developing a medical diagnosis [82–85]. By improving the acquisition of relevant BBN-related schemas, preparatory worked example-based learning should increase the perceived coping resources of medical students tasked with BBN to an SP and should therefore promote a shifting of their stress responses from threat to challenge.

### Hypotheses

The goal of this project is to determine how SAR and WE interventions influence (1) the psychophysiological stress response and (2) the communication-skills performance in medical students tasked with BBN in simulated settings. In addition, we will determine (3) if potential effects on communication performance are mediated by the psychophysiological stress response. Therefore, the study addresses following hypotheses:

H1.1 – Students receiving SAR instructions will exhibit significantly more adaptive, challenge-type psychophysiological responses (i.e., higher resources-demands differential, higher challenge-threat cardiovascular index, higher anabolic balance and higher sAA) than students receiving no SAR instructions.

H1.2 – Students receiving SAR instructions will show significantly better communication skills performance than students receiving no SAR instructions.

H2.1 – Students preparing themselves for the BBN task by learning from a BBN-related worked example will exhibit significantly more adaptive, challenge-type psychophysiological responses than students not preparatorily learning from a BBN-related worked example.

H2.2 – Students preparing themselves for the BBN task by learning from a BBN-related worked example will show significantly better communication skills performance than students not preparatorily learning from a BBN-related worked example.

H3.1 – The challenge-threat resources-demands differential and cardiovascular index are significant mediators of the effect of the SAR intervention on communication skills performance.

H3.2 – The challenge-threat resources-demands differential and cardiovascular index are significant mediators of the effect of preparatory worked example-based BBN learning on communication skills performance.

Furthermore, there are secondary, exploratory issues we want to address with this study. Theory suggests that SAR interventions might also improve mood [39]. However, research on this aspect is inconclusive [61] and the effects of WE on mood have not been investigated previously. Therefore, we treat the effects of SAR and WE on mood as an exploratory issue.

Stress mindsets are global belief systems about the nature of stress [86]. Individuals with a stress-is-enhancing mindset belief that stress is positive and promotes health and performance, whereas individuals with a stress-is-debilitating mindset belief that stress is negative and harms health and performance. By assessing stress mindsets before and after the interventions, we can check if the manipulations affected an individual’s perception of stress (e.g., [57]). This is especially interesting for medical students, since they already have a certain understanding of the functionality of stress responses presented in SAR. Pre-existing stress mindsets might be pivotal for the effectiveness of SAR interventions [67]. One previous study suggests that most cognitive benefits occur when an individual holds a stress-is-enhancing mindset and appraises a stressor as challenge [57]. However, one could also argue that instructing individuals with a stress-is-enhancing mindset to reappraise stress arousal as functional is redundant [67]. Therefore, we will (1) consider stress mindset as a control variable in the primary analysis and (2) analyze stress mindset as a secondary outcome, to evaluate if SAR interventions affect the stress mindset of medical students.

## Methods

### Participants

Participants will be German speaking third-year medical students from Swiss Universities, with no prior experience in BBN. They will be recruited through social media outlets, emails, and direct information in the lecture hall. Exclusion criteria are factors known to affect the psychophysiological outcomes: cardiovascular diseases, neuroendocrine conditions, use of psychotropic drugs or medication, and wearing a pacemaker. Female students additionally cannot participate if they are pregnant or lactating. Participants will be compensated with a monetary reward of 150 Swiss Francs for completing the study, and travel expenses will be reimbursed. Our goal is to collect valid data from 200 participants, to test the hypotheses with the necessary statistical power (see “Sample size calculation” for more details).

### Study design

To test our hypotheses, we will conduct a randomized controlled trial applying a 2 (SAR vs. control) x 2 (WE vs. control) between-subjects design. Participants will be stratified according to gender and randomly assigned to one of four conditions: (1) SAR only, (2) WE only, (3) SAR and WE, (4) no intervention (see Fig. 1). Participants will be blinded to their condition and will not be informed about the various interventions. Raters of the BBN-skills performance will receive video recordings of the BBN situations in a random order with no information about the assigned condition. SPs interacting with the participants will only be present for the BBN situation and will not be informed about which intervention was applied before the encounter. The experimenters will not be blinded, as they are required to set up the corresponding learning modules (including interventions) for each session.

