### Statistical analysis plan

To test the effectiveness of the interventions on communication performance (H1.2, H2.2), we will use 2 (SAR vs. no SAR) x 2 (WE vs. no WE) between-subjects ANOVAs. For the analysis of the repeated psychophysiological stress response outcomes (H1.1, H2.1), we will use linear mixed models with the participants as random effect. To test if the effects of the interventions on communication performance are mediated by the psychophysiological stress response (H3.1, H3.2), we will conduct a bootstrapping mediation analysis following state-of-the-art methodology [101]. We will follow international guidelines to derive the parameters used in the statistical analysis. For each cardiovascular measure, the mean of each 1-minute period will be calculated. For salivary measures, the area under the curve with respect to ground and increase will be computed. Where sensible, we will transform skewed variables to approach normality. We will perform sensitivity analyses with the control variables gender, age, BMI, use of hormonal contraceptives, shift work, SP, stress mindset, depression anxiety and stress, body motion, BBN-related interest & motivation, BBN-related prior experience & skills, and habitual use of emotion regulation strategies. For significance testing, an alpha level of 0.05 will be used.

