### Possible pitfalls

We are aware that the present project is ambitious, which brings several possible challenges.

First, participation in the project will not be part of the regular medical study program but will rather be offered as an extracurricular learning opportunity. Although we assume that medical students have a general interest in communication training, we still rely on voluntary participation.

Second, medical students represent a distinct group of individuals compared to previous SAR-related research. In the third year, medical students already have a solid understanding of the functionality of their stress response, which is a core aspect of SAR interventions. Importantly, a person’s beliefs about stress (i.e., stress mindset) can affect their situation specific stress appraisal [67]. It remains to be seen how the SAR intervention applied in our study will affect the psychophysiology and performance of medical students specifically. We will investigate this issue by assessing participants’ stress mindset before and after the intervention and use it as control variable for primary analyses.

Third, there are more female medical students enrolled in Swiss universities than male students. Gender creates a possible confounder, given the different psychophysiology [87]. To ensure equal allocation to the experimental conditions, participants will therefore be stratified according to gender. Besides, the menstrual cycle of female participants causes monthly fluctuations of steroid hormones, which influence their psychophysiology. To control for these fluctuations, female participants will optimally be tested during the first week after menstruation. This puts restrictions on participation opportunities.

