Lastly, while the BBN scenario is the same for all participants, for feasibility reasons, the SP role will be portrayed by different actors. To minimize any influence from SPs playing their role differently, a professional SP instructor of the Institute for Medical Education will provide detailed and identical training to each SP and ensure comparable acting. Further, SP will be considered as control variable in our statistical analyses. At the same time, because the BBN situation is only simulated, ecological validity could be questioned. Yet, due to the nature of the task, it is not feasible to conduct the experiment with real patients. It has been shown that communication skills performances exhibited in settings with SPs can predict performances in real clinical life [105].

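### Gender stratifies the randomisation but is left out of the primary performance ANOVA, which makes that test conservative and costs some power

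*Protocol article*

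**What the plan says.** Under Study design, the protocol article states: "Participants will be stratified according to gender and randomly assigned to one of four conditions". No other stratification factor is named. Possible pitfalls explains the choice: "Gender creates a possible confounder, given the different psychophysiology".

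Under Statistical analysis plan, the test of communication performance (H1.2, H2.2) is fixed as follows: "we will use 2 (SAR vs. no SAR) x 2 (WE vs. no WE) between-subjects ANOVAs". For the repeated stress-response outcomes (H1.1, H2.1) the text is "we will use linear mixed models with the participants as random effect", and no fixed effects are listed.

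Gender enters the analysis in one sentence of the same section: "We will perform sensitivity analyses with the control variables gender, age, BMI, use of hormonal contraceptives, shift work, SP, stress mindset", followed by further covariates. No part of the article places gender in a primary model.

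SP is in the same sensitivity list. Possible pitfalls adds, without saying which analyses are meant, "SP will be considered as control variable in our statistical analyses".

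**The concern.** Stratifying by a prognostic factor removes its contribution to chance differences between arms. The treatment estimate then varies less from trial to trial. An analysis without the factor does not register this gain. It still counts the gender variance as residual error, so the reported standard error is larger than the real one. Confidence intervals come out too wide, the test rejects less often than its nominal 5% under the null, and part of the power that stratification could deliver is not used.

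This matters because the planned power has almost no reserve, and because the article itself moves the adjusted model to the sensitivity tier. If the two analyses disagreed, the less efficient one would govern.

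**Working it through.** **Inputs from the article (Sample size calculation, Study design).** d = 0.40, two-sided alpha 0.05, target power 0.80, 50 per cell, N = 200, four arms.

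**Inputs assumed.** The share of outcome variance explained by gender, R², is not given; 5%, 10% and 20% are used, with 0 and 30% as outer values. The share of women is not given as a figure; 60% and 70% are used in simulation. Allocation is taken as exactly balanced within gender.

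**Step 1: reproduce the stated sample size.** A main effect in the 2 x 2 design compares two cells with two cells.
- Normal approximation: n per factor level = 2(1.96 + 0.842)² / 0.40² = 98.1, rounded up to 99, so 198 in total.
- Noncentral t at N = 200 (196 df): noncentrality 0.40 × √200 / 2 = 2.828, power 0.804. The smallest N reaching 0.80 is 199, which four equal cells round to 200.

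The stated N = 200 reproduces, for a main effect without covariates.

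**Step 2: size of the unadjusted test.** With total SD 1, the unadjusted analysis reports a standard error of 2/√200 = 0.141. Under balance within gender, the true standard error is 0.141 × √(1 − R²). The null test statistic therefore has SD √(1 − R²), and

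true size = 2[1 − Φ(1.96 / √(1 − R²))].

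- R² = 5%: 1.96 / 0.975 = 2.011, size 0.044
- R² = 10%: 1.96 / 0.949 = 2.066, size 0.039
- R² = 20%: 1.96 / 0.894 = 2.191, size 0.028

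The intervals are wider than necessary by a factor 1/√(1 − R²): 1.026, 1.054 and 1.118.

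**Step 3: power at d = 0.40.**
- Unadjusted (normal approximation): Φ[(2.828 − 1.96) / √(1 − R²)] = 0.813, 0.820, 0.834.
- Adjusted (noncentral t, 195 df, effect 0.40 / √(1 − R²)): 0.823, 0.843, 0.882.

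**Step 4: check by simulation.** N = 200, 40,000 replicates per scenario, exact balance within gender, both models fitted to the same data. Ranges cover the two gender shares.

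| R² | Size, unadjusted | Size, adjusted | Power, unadjusted | Power, adjusted |
|---|---|---|---|---|
| 0 | 0.049 | 0.049 | 0.800–0.806 | 0.800–0.806 |
| 5% | 0.045 | 0.051–0.052 | 0.809–0.811 | 0.824–0.825 |
| 10% | 0.039–0.040 | 0.051–0.052 | 0.813–0.815 | 0.841–0.842 |
| 20% | 0.028–0.029 | 0.049–0.051 | 0.825–0.830 | 0.879–0.884 |
| 30% | 0.018–0.019 | 0.048–0.051 | 0.843–0.845 | 0.919 |

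The simulation agrees with the formulas. Its like-for-like power gain from adjustment is about 0.014–0.015 at 5%, 0.027–0.029 at 10% and 0.054 at 20%.

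**The case against.** **The harm is small and in the safe direction.** This stands. There is no bias and no inflated false-positive rate, and unadjusted power meets the 0.80 target at each R² from 5% upwards. A gender-adjusted analysis is already planned; the dispute is over which analysis is primary.

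**The reason given for stratifying concerns psychophysiology, not communication performance.** This also stands. The one model whose factors are fully listed is the performance ANOVA, and the article does not say that gender predicts performance. If gender explains only 1% or 2%, the Step 2 formula gives a size of 4.9% or 4.8%, which is negligible.

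**The figures assume exact balance within gender in the analysed set.** The article describes no blocking scheme and replaces unusable cases, so the actual effect may be smaller.

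A reader might also draw stronger inferences, which the article does not support:
- *That the mixed models certainly omit gender, at the same cost.* Their fixed effects are not listed at all, so the omission is inferred from gender appearing only in the sensitivity sentence. Other sections place some control variables (stress mindset, session measures) in the primary analyses, so that section may not be the full specification. The figures above come from a single-measure comparison. In a repeated-measures model the participant effect absorbs a stable gender difference, so within-participant contrasts gain less.
- *That the same loss applies to SP.* SP is not a stratification factor, and nothing in the article balances actors across arms. The size formula needs a factor balanced by design; without that, the unadjusted test keeps roughly its nominal size.
- *That the article contradicts itself on SP.* A sensitivity analysis is a statistical analysis, so the two statements are compatible.

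**Conclusion.** The point holds for gender and the primary performance ANOVA. The article stratifies by gender, fixes a primary performance model without it, and assigns it to sensitivity analyses. If allocation is balanced within gender and gender explains 5% to 20% of performance variance, the true size falls to between about 4.4% and 2.8%, and about 0.01 to 0.05 of power is forgone. With no gender effect the loss is essentially nil. For the mixed models the same recommendation applies, with less certainty about the omission and a smaller gain for within-participant contrasts. The result is conservative inference and lost precision. It does not make the planned analysis invalid or the sample size wrong. It is worth correcting because the correction is nearly free.

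**What to change.** Specify the primary performance model as SAR + WE + SAR x WE + gender, and keep the unadjusted 2 x 2 ANOVA as a sensitivity analysis. State gender as a fixed effect in the primary mixed models too. Adjustment for SP can stay among the sensitivity analyses.

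The cost is a change of wording and one degree of freedom (196 to 195 in the performance model). Gender is already collected in the online entry questionnaire, so no new data are needed, and N = 200 need not rise.
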